### Sample size calculation

Group A/B in the randomized withdrawal trial: According to a 2018 IPD meta-analysis [7] and our previous study [14], we assumed that two groups (A and B) have an assumed favorable outcome rate of 73%. Taking into consideration various parameters like a 90% FR-6 rate, a 1:1 random assignment to two different durations (month 6 or month 9), a 15% margin of non-inferiority, a one-sided significance level of 5%, 80% power, and a 20% drop rate, 304 participants are needed for each group. Hence, 304 + 304 = 608 participants in total for groups A and B.

Calculation for Group C/D in the single-arm trial: Two other groups (C and D) have an assumed favorable outcome rate of 57% [7, 14]. Using the same parameters (15% margin of non-inferiority, a one-sided significance level of 5%, 80% power, and a 20% drop rate), 85 participants are needed for each group. Hence, 85 + 85 = 170 participants in total for groups C and D.

Combining both sets of groups, the total sample size required would be 608 + 170 = 778 participants for the SEAL-MDR study.

### Statistical analysis

Efficacy outcomes will be evaluated using modified intention-to-treat (mITT) and per protocol (PP) approaches, focusing on mITT. The safety analysis includes all participants receiving at least one dose of study drugs. The mITT group consists of those randomized and treated at least once, while the PP group comprises mITT members who complete > 80% of planned treatment and adhere to the protocol.

Analysis is performed in SPSS 26.0. Categorical data are presented as counts and percentages, and continuous data as means (standard deviations, SD) and medians (interquartile range, IQR). Depending on data distribution, Student’s t-test or non-parametric tests are used for continuous variables, and Chi-square or Fisher’s test for categorical ones. Primary analysis estimates unfavorable outcome rates in subgroups of Regimens A and B, with 95% CI for each group. Kaplan-Meier and Cox models evaluate time to unfavorable outcomes and culture conversion. Variables with *P* < 0.1 in univariate analysis and clinical significance are incorporated into a multivariate model. A *P* < 0.05 is considered significant.

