## Methods

### Trial design and oversight

We are conducting a two-part, patient-stratified, treatment-response-guided study: a randomized withdrawal trial for MDR-TB and a single-arm trial for pre-XDR-TB (Fig. 1; Table 1). For MDR-TB, patients are assigned to either Regimen A (Bdq, Lzd, Mfx, Cs) or Regimen B (Lzd, Mfx, Cs, Cfz, Pza) based on treatment preference and FQ drug susceptibility tests (DST). Compared to our previous study, Pza is deleted from Regimen A. For pre-XDR-TB, we employ Regimen C (Bdq, Lzd, Cs, Cfz, Pza) and Regimen D (Lzd, Cs, Cfz, Pza, SASP). Each regimen lasts 6–9 months. Post-6 months, participants in Groups A and B are subdivided into 6-month and 9-month treatment durations based on randomization, while those in Groups C and D are similarly divided based on clinical judgment. For the randomized withdrawal trial, the primary hypothesis is that the 6-month regimen will be non-inferior to the 9-month regimen in terms of unfavorable outcomes.

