**Fig. 1 Fig1:**
[figure not shown]
The flow diagram of the SEAL-MDR study. The diagram outlines the key steps in the study, starting with patient recruitment, followed by initial selection of treatment regimens based on *M. tuberculosis* drug resistance spectrum and patient preferences. For the randomized withdrawal trial, patients with a favorable treatment response will be randomized to 6 or 9 months of treatment after 6 months of treatment. Participants with a poor treatment response will not be randomized but will continue on a 9-month treatment regimen. In the single-arm trial, participants with a favorable response will stop treatment at month 6, otherwise treatment will be extended to 9 months. Throughout the study, FQ resistance results may be obtained at various stages to guide initial and subsequent regimen adjustments. Participants will attend visits at 12 months post-treatment to obtain primary and secondary endpoints. (Abbreviations in this figure: Bdq: bedaquiline; Cfz: clofazimine; DST: Drug susceptibility testing; FQ: fluoroquinolone; Lzd: linezolid; Mfx: moxifloxacin; Pza: Pyrazinamide; Rif: rifampicin; SASP: Sulfasalazine; TB: tuberculosis)

**Table 1 Tab1:** Trial regimens

FQ susceptibility	Regimen	Drugs	Durations
MDR-TB	A	bedaquiline, linezolid, moxifloxacin, cycloserine and pyrazinamide	6–9 months
	B	linezolid, moxifloxacin, cycloserine, clofazimine and pyrazinamide	6–9 months
Pre-XDR-TB	C	bedaquiline, linezolid, cycloserine, clofazimine and pyrazinamide	6–9 months
	D	linezolid, cycloserine, clofazimine, pyrazinamide and salazosulfapyridine	6–9 months

This study, named SEAL-MDR, was registered with the Chinese Clinical Trials Registry and has received ethical approval from participating hospitals. Written informed consent will be obtained from all adult participants or their legal guardians by trained medical personnel who may be an investigator, clinician, or designated nurse experienced in explaining the elements of clinical trials.

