### Randomization, enrolment and follow-up

Before initiating treatment, all available DST results (e.g., Xpert, gDST, pDST) are employed to triage patients with MDR-TB and pre-XDR-TB. Considering variables such as regimen affordability and past adherence, MDR-TB patients are allocated to either Regimen A or B (Table 1). Regimen B is preferred for uninsured participants, those concerned about drug costs, and individuals willing to accept potential skin discoloration caused by Cfz. Pre-XDR-TB patients are allocated to either Regimen C or D, with Regimen D being better suited for those without insurance coverage and lesser financial means.

Should post-entry DST results confirm resistance to any study drug, treatment regimens will be adjusted according to established clinical practice principles in our previous studies [1]. For example, If initial gDST is unavailable and later pDST reveals FQ resistance 2–3 months post-enrollment, participants will transition from Regimens A/B to C/D, incorporating the prior treatment duration into the revised 6-month course. In certain scenarios, participant withdrawal may be necessitated. For example, participants unwilling to switch sill be prescribed long-course treatment and excluded from the study.

Participants initially undergo a 6-month treatment course. A blinded mid-point review committee evaluates clinical events and favorable treatment responses during the sixth-month visit (FR-6, Table S2). This assessment includes sputum culture conversion at month four, adequate drug intake at month six (excluding those who received less than ~ 90% of study doses), and chest computed tomography (CT) stabilization. Participants having a FR-6 will be centrally randomized into either a 6- or 9-month treatment group via MedSci RTSM Cloud Platform (rtsm.medsci.cn). Otherwise, they will continue their current regimen until month nine. Failure to convert by the eighth month necessitates an extension to an 18–20 month regimen, marking it as a treatment failure.

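### Both efficacy analysis sets require randomization, so none of the 170 Group C/D participants falls in one, and month-6 response in Groups A/B becomes 100% by construction

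*Protocol article*

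**What the plan says.** Four parts of the protocol article bear on this.

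- **Analysis sets (Statistical analysis).** "Efficacy outcomes will be evaluated using modified intention-to-treat (mITT) and per protocol (PP) approaches, focusing on mITT". The sets are then defined: "The mITT group consists of those randomized and treated at least once, while the PP group comprises mITT members" with adequate completion and adherence. The same paragraph uses a different rule for safety: "The safety analysis includes all participants receiving at least one dose of study drugs".
- **Who is randomized (Trial design and oversight; Randomization, enrolment and follow-up; Fig. 1 legend).** Group A and B participants with FR-6 are randomized at month 6 to 6 or 9 months in total. For A/B participants without FR-6: "Otherwise, they will continue their current regimen until month nine". The design section says of the other part: "while those in Groups C and D are similarly divided based on clinical judgment". The Fig. 1 legend adds: "In the single-arm trial, participants with a favorable response will stop treatment at month 6, otherwise treatment will be extended to 9 months". Entry to Regimen C or D is also not random; insurance and means are considered.
- **What C/D are sized for (Sample size calculation).** A 57% favorable rate, a 15% margin, one-sided 5%, 80% power and 20% dropout give 85 per group: "Hence, 85 + 85 = 170 participants in total for groups C and D".
- **Outcomes (Outcome measures).** The primary outcome is made up of failure, loss to follow-up and death. Secondary outcomes include culture conversion by month 2 and FR-6 itself, both settled before or at the moment of randomization.

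**The concern.** A set defined by randomization cannot describe a part of the trial in which nobody is randomized. The single-arm part has its own powered criterion and is the vehicle for judging the sulfasalazine regimen, yet neither efficacy set can hold its participants. Whoever analyses Groups C and D must supply a population that the plan does not name, possibly after outcomes are known.

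In Groups A and B the definition suits the duration comparison but not outcomes that precede randomization. Since FR-6 is the entry condition for randomization, an FR-6 rate computed among the randomized carries no information. Month-2 culture conversion would be reported only among people already selected for responding well.

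**Working it through.** **1. The plan's own sample sizes reproduce, so the C/D efficacy criterion is intended.**

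Groups C/D: p = 0.57, margin 0.15, one-sided 5%, power 80%, dropout 20%, all from Sample size calculation.

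n = p(1 − p)(z₀.₉₅ + z₀.₈₀)² / margin² = 67.35, rounded up to 68. Then 68 / 0.80 = 85 per group, as stated, and 2 × 85 = 170.

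Groups A/B: 73% favorable in both durations, margin 0.15, the same error rates, FR-6 rate 90%. This gives 109 per duration arm; 109 / 0.80 is 137 after rounding up; 2 × 137 / 0.90 = 304.4, against the stated 304 per regimen.

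**2. Membership of the sets under the stated rules.**

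| Participants | Randomized? | In mITT or PP? | In safety set? |
|---|---|---|---|
| A/B with FR-6 | Yes, at month 6 | mITT yes; PP if criteria met | Yes |
| A/B without FR-6, or dead or lost before month 6 | No | No | Yes, if dosed |
| C/D, all | No | No | Yes, if dosed |

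C/D in an efficacy set: 0 of 170. Share of the trial: 170 / 778 = 21.9%.

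**3. Effect on A/B outcomes that precede randomization.**

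Planned participants without FR-6: 608 × (1 − 0.90) = 60.8, about 61. Planned with FR-6: 608 × 0.90 = 547.2. Every member of the mITT set has FR-6, so the FR-6 rate in it is 547/547 = 100% whatever the regimens do. Month-2 conversion loses the same 61 or so, together with any early deaths or losses not already in that count.

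**4. Conditional illustration: a set of month-6 responders used for C/D.**

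The document does not propose this. If a share x left before month 6, all with unfavorable outcomes, and were dropped, a true rate of 57% would appear as 0.57 / (1 − x):

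| x | Apparent favorable rate |
|---|---|
| 5% | 60.0% |
| 10% | 63.3% |
| 15% | 67.1% |
| 20% | 71.3% |

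x is an assumption. The document gives no early-exit rate for C/D.

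**The case against.** **This is a condensed article, and analysis sets are often settled in the full protocol or SAP.** That would answer a missing definition. Here a definition is given, it is tied to efficacy outcomes without exception for the single-arm part, and it does not fit that part. The safety sentence shows that an all-treated wording was at hand.

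**C/D outcomes can still be classified.** True. The outcome definitions apply to them and they are in the safety set. What is lacking is a stated denominator for efficacy, so it would be too strong to say that the single-arm part can yield no result.

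**Leaving non-randomized A/B participants out is inherent to randomized withdrawal.** This stands for the primary comparison, whose hypothesis concerns 6 versus 9 months. It does not stand for FR-6 and month-2 conversion.

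**A reader might infer that the C/D test will run well above its 5% error.** Take 42% as the bar (57% minus 15%, a reading the document does not spell out). With all 85 counted, the exact error is 4.4% (44 or more favorable). Suppose a share x is removed, of whom a fraction u are unfavorable. The remaining rate is (0.42 − x(1 − u)) / (1 − x), and the chance of passing is:

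| Removed | u = 100% | u = 75% | u = 58% |
|---|---|---|---|
| 10% (76 left, 40 needed) | 17.7% | 7.8% | 4.0% |
| 20% (68 left, 36 needed) | 52.0% | 16.2% | 4.5% |

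Starting from 68 evaluable, the u = 100% figures are 15% and 38%. The documents do not support the high values. No section proposes a responder set for C/D. The 90% FR-6 rate is stated for A/B only. Participants without a favorable month-6 response are continued to month 9 and are not classed as unfavorable for that reason; FR-6 can also be missed through drug intake or CT findings.

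**A reader might also see a contradiction with the primary outcome being timed from initial assignment.** That phrase fixes when the outcome is determined, not who is analysed.

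**Conclusion.** The point holds as a conflict between a stated definition and the design. No efficacy set in the article contains any of the 170 C/D participants (21.9% of 778), although each group is sized for a powered efficacy criterion. In A/B, FR-6 is 100% by construction, and about 61 of 608 planned participants are left out of outcomes that precede randomization. These figures rest only on the stated definitions, the planned sizes and the planned 90% FR-6 rate.

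Restricting the A/B duration comparison to randomized participants is correct and is no part of the criticism. Bias in the C/D favorable rate is a risk only if a month-6 responder set were chosen. Its direction would be upward if early exits are predominantly unfavorable, but its size cannot be fixed from the document.

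**What to change.** In the Statistical analysis section:

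1. Keep the present mITT and PP definitions, and state that they apply to the A/B 6- versus 9-month comparison.
2. For Groups C and D, define the primary efficacy set as all participants who received at least one dose of the assigned regimen, counted from first dose. Failure, loss or death before month 6 is scored under the existing outcome definitions. Draw the C/D PP set from this set.
3. State how participants who switch from Regimen A or B into C or D after a late fluoroquinolone result are counted. The article carries their prior treatment time into the new course, so the starting point for counting needs a rule.
4. Analyse FR-6, month-2 culture conversion and other pre-randomization outcomes for A/B in all treated participants.

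The cost is a few sentences and one additional table, with no new data collection. The reported rates will probably be somewhat less favorable than among responders alone. The change should be dated before C/D outcomes are analysed, so that the choice of population cannot be linked to the results.

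### The per-protocol completion threshold is counted over the whole course, although the randomised arms differ only in months 7-9

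*Protocol article*

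**What the plan says.** The Protocol article defines its efficacy sets under Statistical analysis. The general approach is: "Efficacy outcomes will be evaluated using modified intention-to-treat (mITT) and per protocol (PP) approaches, focusing on mITT". The parent set is defined first: "The mITT group consists of those randomized and treated at least once". Within it, "the PP group comprises mITT members who complete > 80% of planned treatment and adhere to the protocol". The percentage is not tied to any part of the course, and the article does not say what the adherence condition covers.

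The timing of randomisation is given in the Fig. 1 legend: "patients with a favorable treatment response will be randomized to 6 or 9 months of treatment after 6 months of treatment". Under Randomization, enrolment and follow-up, the month-6 favourable response (FR-6) needed for randomisation includes "adequate drug intake at month six (excluding those who received less than ~ 90% of study doses". That section then states: "Participants having a FR-6 will be centrally randomized into either a 6- or 9-month treatment group".

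Under Trial design and oversight, "the primary hypothesis is that the 6-month regimen will be non-inferior to the 9-month regimen in terms of unfavorable outcomes". Groups C and D are not randomised. Their duration follows clinical judgement.

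**The concern.** In a non-inferiority comparison, poor adherence to the longer course makes the two durations look alike and so favours the shorter one. A per-protocol analysis is run partly to guard against this. It can do so only if its adherence rule examines the treatment that separates the arms.

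Here that treatment is months 7-9. The rule instead counts the whole course, most of which was taken before randomisation and was already screened for intake. Two consequences follow:

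- Participants in the 9-month arm who took much less than the three extra months can stay in the per-protocol set, which narrows the contrast.
- A 9-month participant who dies or is lost soon after randomisation can fail the threshold and leave the set along with an unfavourable outcome. A 6-month participant with the same event at the same time passes it.

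The first effect pulls towards no difference. The second flatters the 9-month arm. Their net direction cannot be told in advance, so agreement between the per-protocol and mITT results would be hard to interpret.

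Under-treatment in months 7-9 is plausible. The section Treatment of patients says that drugs are not free and that directly observed treatment is not used.

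**Working it through.** **The plan's own figures.** The article gives no number for this rule beyond the threshold. Its sample size for each of Groups A and B does reproduce from its stated inputs: 2 × 0.73 × 0.27 × (1.645 + 0.842)² / 0.15² = 108.3, so 109 per arm; 109 / 0.8 = 136.3, so 137 per arm; 2 × 137 / 0.9 = 304.4, against 304 stated. The sample size is not at issue.

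**Inputs**
- Planned treatment: 6 or 9 months, as randomised.
- Randomisation after month 6, so the randomised difference is 9 − 6 = 3 months.
- Share of the first six months' doses taken, f: about 0.90 to 1.00, from the FR-6 condition.
- Completion threshold: strictly more than 80% of planned treatment.
- Unit: months' worth of prescribed doses, each month weighted equally. This is an assumption. The article does not say how completion is counted across drugs, and bedaquiline is not given daily after its first two weeks.

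**6-month arm.** Completion at randomisation is 6f / 6 = f, that is 90% to 100%. Everyone is above 80%. A 6-month participant who went on to take nine months would score 9 / 6 = 150% and also pass this test.

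**9-month arm.** Completion at randomisation is 6f / 9. The threshold in months is 0.80 × 9 = 7.2. The amount still needed is more than 7.2 − 6f, and the share of the three months that can be missed is less than (3 − (7.2 − 6f)) / 3.

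| f | Complete at randomisation | Extra months needed (more than) | Share of 3 months that can be missed (less than) |
|---|---|---|---|
| 0.90 | 5.4 / 9 = 60.0% | 7.2 − 5.4 = 1.8 | 1.2 / 3 = 40% |
| 0.95 | 5.7 / 9 = 63.3% | 7.2 − 5.7 = 1.5 | 1.5 / 3 = 50% |
| 1.00 | 6.0 / 9 = 66.7% | 7.2 − 6.0 = 1.2 | 1.8 / 3 = 60% |

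The better the earlier adherence, the less of the randomised treatment is required.

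**Sensitivity to the approximate gate.** If 85% intake were let through, the 6-month arm would still all pass. A 9-month participant would need more than 7.2 − 5.1 = 2.1 months and could miss up to 0.9 / 3 = 30%.

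**Early events.** With full intake after randomisation, a 9-month participant who dies or is lost within about 1.2 months (f = 1.00) or 1.8 months (f = 0.90) of randomisation has not passed 7.2 months and fails the threshold. Death and loss to follow-up are components of the primary outcome (Outcome measures).

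**Alternatives**
- More than 80% of months 7-9: more than 0.80 × 3 = 2.4 months needed, so less than 0.6 month (20%) can be missed. Total intake would exceed 5.4 + 2.4 = 7.8 to 6.0 + 2.4 = 8.4 months, instead of 7.2.
- Raising the whole-course threshold to 90%: 0.90 × 9 = 8.1; 8.1 − 5.4 = 2.7 and 8.1 − 6.0 = 2.1 months needed, so 10% to 30% could still be missed. A higher threshold on the same base is therefore the weaker repair.

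**The case against.** The strongest reply is that the threshold is only half of the definition. The other half, adherence to the protocol, could remove a 9-month participant who stops early without cause, or a 6-month participant who carries on past month 6. The supplementary tables on FR-6 (Table S2) and on treatment interruptions (Table S6) are not shown and could narrow the gap, for example through make-up doses. This stands as a limit on the point. A reader might infer that the whole per-protocol rule is met by every 6-month participant at randomisation, or that adherence exclusions in that arm are zero. The documents support this for the completion threshold only. On the other hand, if the adherence condition barred every missed dose, a percentage threshold would be redundant, so the percentage is best read as the operative dose criterion.

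Three further objections have weight:

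- The 40-60% is a bound. A reader might take it as the expected shortfall, but the article gives no figure for how many 9-month participants would complete only part of months 7-9. Those randomised have already shown good intake, and a staff member verifies and records consumption.
- The per-protocol analysis is supportive. The article puts its focus on mITT, so the main conclusion does not rest on this set.
- Part of the one-arm exclusion is inherent. One arm stops when it is randomised and has no later doses to miss, so any dose-shortfall rule acts on the other arm alone. A reader might blame the imbalance wholly on the 80% rule. That would be wrong, and the fix does not remove it.

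It may also be said that a condensed article leaves such detail to the analysis plan. That covers the meaning of the adherence condition. It does not cover the threshold, which the article states and which fits a trial randomised at baseline better than this one.

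**Conclusion.** The point holds for the completion threshold. As stated, it excludes nobody in the 6-month arm, and in the 9-month arm it is met with just over 1.2 to 1.8 of the three randomised months. At worst, someone counted as per protocol has missed 40-60% of the treatment under test. This rests on planned treatment meaning the assigned 6 or 9 months, on an FR-6 gate of about 90%, on months being weighted equally, and on the adherence condition and the unseen tables not removing such participants.

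The consequence is a weaker supportive check on non-inferiority. No bias in the risk difference can be computed from the article, and the documents do not support a claim that the mITT comparison is compromised. The change is worth making but is not critical.

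A secondary point concerns the mITT definition. It requires randomisation, which Groups C and D never undergo, although the Sample size calculation section sizes them on an efficacy rate. Read literally, it gives them no efficacy set. A reader might infer that no efficacy analysis of these groups is planned. Their sample size argues against that, and the full plan may define their set.

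**What to change.** Amend the wording of the analysis sets before the data are analysed:

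1. In the 9-month arm, apply the per-protocol completion threshold to the doses due in months 7-9. The existing level of more than 80% is enough.
2. In the 6-month arm, count study treatment continued beyond the assigned stop as a per-protocol deviation.
3. Do not exclude a participant whose shortfall results from death or another primary-outcome event.
4. Limit the mITT definition to Groups A and B, and state the efficacy set for Groups C and D as all participants who took at least one dose.

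These changes affect who is analysed, not how anyone is treated. The treatment cards described under Treatment of patients already record intake, so no new data are needed. The cost is wording and a somewhat smaller 9-month per-protocol set. How much smaller cannot be estimated from the article. Some exclusion from the 9-month arm alone will remain, so the numbers and reasons for exclusion should be reported by arm.

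### The stated primary analysis (separate unfavorable rates, each with a 95% CI) does not test the 6- versus 9-month non-inferiority hypothesis for which the trial was sized

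*Protocol article*

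**What the plan says.** Three parts of the protocol article bear on the primary comparison.

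- **Trial design and oversight** states that "the primary hypothesis is that the 6-month regimen will be non-inferior to the 9-month regimen in terms of unfavorable outcomes". It also says that Groups A and B are split by randomisation into 6- and 9-month durations.
- **Sample size calculation** sizes each of Regimens A and B at 304, assuming 73% favorable, 90% reaching a favorable month-6 response (FR-6), 1:1 allocation, and "a 15% margin of non-inferiority, a one-sided significance level of 5%, 80% power, and a 20% drop rate".
- **Statistical analysis** defines the primary analysis in one sentence: "Primary analysis estimates unfavorable outcome rates in subgroups of Regimens A and B, with 95% CI for each group". The same section lists chi-square or Fisher tests for categorical variables, Kaplan-Meier and Cox models for time to event, and a general threshold of P < 0.05 with no sidedness given.

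The Outcome measures section counts loss to follow-up as part of the unfavorable outcome and excludes only participants who are not assessable from the primary analysis.

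**The concern.** A non-inferiority claim needs three things: an estimate of the difference between the arms, a confidence limit for it, and a comparison of that limit with the margin. The sentence that defines the primary analysis has none of them. Since Groups A and B are divided by duration, the natural reading of subgroups is the 6- and 9-month arms, each with its own rate and interval.

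The other methods in the section do not fill the gap. Chi-square, Fisher and Cox tests ask whether the arms differ, and a non-significant result does not show that 6 months is within 15 points of 9 months. A reader working from this section would have no stated rule for declaring non-inferiority, and a shorter regimen could be accepted or rejected under a criterion chosen after the data are seen.

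**Working it through.** **Inputs** (Sample size calculation): 73% favorable, so 27% unfavorable, in both durations; margin 15 points; one-sided 5%; 80% power; 20% dropout; 90% FR-6; 1:1 allocation. The article does not name the scale of the margin. The risk-difference scale is assumed because it reproduces the stated number.

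**1. The plan's own figure.**

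n per arm = (z_alpha + z_beta)² × 2 × p(1 − p) / margin²
= (1.645 + 0.8416)² × 2 × 0.73 × 0.27 / 0.15² = 108.3, so 109.

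- Two arms: 218 evaluable.
- Dropout: 218 / 0.8 = 272.5, so 273.
- FR-6: 273 / 0.9 = 303.3, so 304 per regimen, as stated.

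At one-sided 2.5% the same formula gives 137.5, so 138 per arm, and 276 / 0.72 = 383.3, so 384 per regimen. The sizing therefore did use one-sided 5%, which corresponds to a two-sided 90% CI for the difference.

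**2. What the stated analysis delivers.** With 109 per arm and 27% unfavorable, each separate 95% CI has a half-width of 1.96 × √(0.27 × 0.73 / 109) = 8.3 points. Two such intervals, side by side, contain no test against 15 points.

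**3. What the hypothesis requires.** The standard error of the difference is √(2 × 0.27 × 0.73 / 109) = 6.0 points.

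| Interval for the difference | Half-width | Largest observed excess that passes |
|---|---|---|
| Two-sided 90% | 9.9 points | 15 − 9.9 = 5.1 points |
| Two-sided 95% | 11.8 points | 15 − 11.8 = 3.2 points |

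An observed excess between 3.2 and 5.1 points passes or fails depending on a level that the article does not set for the difference.

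**4. Why a difference test cannot stand in.** Suppose 29/109 (26.6%) unfavorable at 9 months and 41/109 (37.6%) at 6 months. The excess is 11.0 points, with standard error √((0.266 × 0.734 + 0.376 × 0.624) / 109) = 6.3 points. Then z = 11.0 / 6.3 = 1.75, and two-sided P is about 0.08, which is not significant. The upper 90% limit is 11.0 + 1.645 × 6.3 = 21 points, well past the margin.

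**5. Power, if the level for the difference were 95%.** Power = Φ(0.15 / √(2 × 0.73 × 0.27 / n) − z).

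| Evaluable per arm | 90% CI (z = 1.645) | 95% CI (z = 1.960) |
|---|---|---|
| 109 (all 20% dropout excluded) | 80.2% | 70.3% |
| 304 × 0.9 / 2 = 136.8 (no exclusions after randomisation) | 87.5% | 79.8% |

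A simulation of the Wald interval at 109 per arm gave 80.5% and 71.0%, in agreement with the first row.

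**The case against.** The strongest reply is that this is a journal article condensing a fuller protocol. The effect measure and the interval method are commonly left to the protocol or the SAP. The hypothesis, margin and alpha are all stated, and the rates being estimated are the inputs to the required difference. This has weight: it would be too strong to say that the trial cannot answer its question. It does not clear the sentence. The article does not stay silent on the primary analysis; it defines one, and that definition does not match its own hypothesis and sizing. The phrase might have been meant as an interval for the difference within each regimen, but the text does not say so.

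Two stronger readings are tempting and should be resisted.

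- **That the trial has only 70% power.** The article attaches the 95% CI to group rates. A 95% CI on a single rate does not conflict with a one-sided 5% test of a difference, and no power is lost by reporting it. The 70% figure arises only if a two-sided 95% CI of the difference is judged against the margin and the full 20% dropout leaves the analysis. Loss to follow-up counts as unfavorable, so many of those participants would stay in the denominator.
- **That a two-sided P < 0.05 is the decision rule.** The article gives no sidedness, and it ties neither the threshold nor the chi-square and Fisher tests to the primary endpoint. Nothing shows that the investigators intend to read P > 0.05 as non-inferiority.

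**Conclusion.** The point holds as a mismatch between the defined primary analysis and the primary hypothesis. Separate rates with separate intervals do not test whether 6 months is within 15 points of 9 months at one-sided 5%, and the general tests listed cannot do so either. This rests on the text and needs no assumption beyond the ordinary reading of the sentence.

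The sample size is not in error: 304 per regimen follows from the stated inputs. Any power loss is conditional. If a 95% CI of the difference were the criterion, per-regimen power would lie between about 70% and about 80%, depending on how much of the 20% dropout leaves the analysis. Both ends assume a true unfavorable rate of 27% in each arm, and the upper end assumes that this rate holds with lost participants counted as unfavorable. The range applies to each regimen separately, as the trial was sized. Pooling A and B (608 × 0.72 / 2 = about 219 per arm) would give about 94%, but the article does not describe that as the sized comparison.

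**What to change.** Replace the primary-analysis sentence with a rule that matches the hypothesis:

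1. Within each of Regimens A and B, the primary analysis is the risk difference in unfavorable outcome, 6 minus 9 months, in randomised participants.
2. Non-inferiority is declared if the upper confidence limit of that difference is below 15 points.
3. Use the two-sided 90% CI, which matches the one-sided 5% sizing. If a 95% CI of the difference is used instead, restate the per-regimen power as about 70% (109 evaluable per arm) to about 80% (about 137 per arm). Holding 80% with the full dropout excluded would need 138 per arm, about 384 per regimen.
4. State that P < 0.05 tests for a difference are not the primary criterion. The per-group rates with 95% CIs can stay as description.

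The cost is wording in the protocol and any SAP. No extra patients are needed unless the sponsor chooses the 95% level and wants 80% power under full dropout. The criterion should be fixed before outcomes are compared by duration.
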